### Participants' Timeline

A summary of participants' timeline is shown in Table 1.

**Table 1 T1:** Assessment schedule.

	**Study period**				**Endpoint**	**Unscheduled medical examination (appearance of skin rash, etc.)**	**When the study intervention is discontinued (including when atopic dermatitis is diagnosed)**
**Visit**	**1**	**2**	**3**	**4**	**5**		
**Time point (visit windows)**	**Entry (6 days old)**	**4 weeks after entry (±7 days)**	**12 weeks after entry (±14 days)**	**24 weeks after entry (±28 days)**	**32 weeks after entry (±28 days)**		
**ENROLLMENT**							
Eligibility screen	X						
Informed consent	X						
Allocation	X						
**ASSESSMENTS**							
Background information	X						
Living environment	X				X		X
Nutrition	X				X		X
Body height	X	X	X	X	X	X	X
Body weight	X	X	X	X	X	X	X
Evaluation of the presence or absence of atopic dermatitis by a blinded physician	X	X	X	X	X	X	X
EASI score by a blinded physician		X	X	X	X		X
POEM score by caregivers		→	→	→	→		→
Stratum corneum hydration	X	X	X	X	X		X
Total IgE, egg white, ovomucoid, milk, wheat, peanut, and *Dermatophagoides farinae*-specific IgE and TARC in serum					X		X
Check the diary		X	X	X	X	X	X
Amount of emollients used		X	X	X	X	X	X
Combination therapy		X	X	X	X	X	X
Adverse events		X	X	X	X	X	X

*EASI, Eczema Area and Severity Index; POEM, patient-oriented eczema measure; TARC, thymus and activation-regulated chemokine; IgE, immunoglobulin E*.

### Sample Size Calculation

A total of 60 participants, with 20 in each group, will be enrolled in this study. This is an exploratory study, and the target case size was selected based on the research period and available resources (feasibility). In our institute, the number of births exceeds ~2,000 per year, and the number of singletons born at 37 weeks after pregnancy is ~1,200 per year. An epidemiological study of AD in Japan showed that the overall AD prevalence was 6.9%. Moreover, the AD prevalence was 9.8, 8.7, 4.4, and 2.6%, respectively, for those in their 20, 30, 40, and 50/60s. The results showed that AD prevalence was higher in women than in men (9.3 vs. 5.1%) (16). Recently, a Japanese national cohort study showed that maternal AD diagnosis was found in 15.7% of mothers (17). Therefore, recruiting 60 neonates within the 8-month registration period should be possible.

### Recruitment

We will place posters and pamphlets around the examination room at our institute. We will perform provisional enrollment and make a list if parents are willing to participate in the study and the offspring may meet the inclusion criteria. When a tentatively listed pregnant woman gives birth, we will reconfirm that the selection criteria are met and recruit the woman.

### Assignment of Interventions: Allocation

#### Sequence Generation

Participants will be randomly assigned in a 1:1:1 to groups A, B, and C using permuted block randomization. A computer-generated allocation sequence will be created by the study statistician using SAS PROC PLAN. The block size is masked from all except the statistician to ensure allocation concealment.

#### Concealment Mechanism/Implementation

We will use VIEDOC4 (Pharma Consulting Group Japan K.K., Tokyo, Japan) for enrollment for this study, and will enroll the subjects and randomize them. The participant's identification number and the assigned group will be displayed on electronic data capture, and a registration confirmation notification will be automatically sent to the study physicians and the data center by email. The study physicians will print and store the registration confirmation notification email.

### Assignment of Interventions: Blinding

#### Who Will Be Blinded

This study separates outpatient physicians from skin-assessment physicians. The physicians who measure EASI and diagnose AD (i.e., evaluate only the skin and do nothing else) will be blinded to the group allocations and will not look at documents and any other information about the study intervention. We will also instruct participants not to reveal which group they are assigned to when they have a skin evaluation. The two moisturizers are both colorless and odorless. A separate person will assess the amount of remaining topical product to determine how much product was applied.

### Data Collection and Management

#### Plans for Assessment and Collection of Outcomes

A summary of the data collection plan is shown in Table 1. Background information, the living environment, and nutrition will be provided by interview. Adherence and POEM scores will be obtained from the diary. The EASI score and the diagnosis of AD will be obtained via physical examination by a blinded physician.

### Data Management

The electronic data capture system will be used for data in this study. All data management will be performed independently by the data center of the NCCHD.

### Confidentiality

During conducting research, the staff involved in the study will establish safety management and systems to protect personal information. All data of the participants who withdrew the consent will be discarded; however, the other data will be stored in VIEDOC infrastructure according to “methods in analysis to handle protocol non-adherence and any statistical methods to handle missing data,” which is hosted in data centers with state-of-the-art surveillance and access control, redundant internet and power feed, and protection against theft, fire, and natural disasters. The data of the participants will be used for the phase III study.

### Plans for Collection, Laboratory Evaluation, and Storage of Biological Specimens for Genetic or Molecular Analysis in This Trial/Future Use

The study physicians will properly store the samples obtained in this study until 5 years after the study is completed.

### Statistical Methods

#### Statistical Methods for Outcomes

Analysis will be performed according to the intention-to-treat principle. To assess whether group A or group B is more effective than group C in preventing the onset of AD, we will use two co-primary analyses using the log-rank test for the time to the onset of AD. The significance level of each comparison is 2.5%. For each group, Kaplan–Meier estimates of the AD-free rate will be determined. Additionally, the Cox proportional hazards model will be used to estimate the hazard ratios of groups A vs. C and groups B vs. C, and their 95% CIs. The CIs will be calculated using the Wald type method. The exact method will be applied to adjust for tied observation times. A test with Schoenfeld residuals will be used to assess the proportional hazard assumption. If a significance level of 10% rejects the validity of the proportional hazards assumption, group comparisons using the difference in the restricted mean survival time will be applied as a supplementary analysis of the co-primary analysis. For the secondary endpoints, the mean and standard deviation of continuous variables, and the frequency and proportion of discrete variables will be calculated for each treatment group and time point. For the safety endpoints, the frequency and proportion of adverse events occurring will be calculated for each treatment group.

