In 2014, we performed a randomized, controlled trial (RCT) to evaluate whether moisturizer (2e, Shiseido Japan Co., Ltd., Tokyo, Japan) once daily prevents the incidence of AD at 32 weeks of age compared with a control group in which Vaseline was applied as required from birth (9). This study was a definitive trial, and 118 neonates participated showed that the cumulative incidence of AD was significantly lower in the 2e application group compared with the control group (hazard ratio: 0.48, 95% CI: 0.27–0.86). Recently, Chalmers et al. (10) reported that application of the moisturizer Doublebase Gel (Dermal Laboratories, Herts, UK) or Diprobase Cream (Bayer, Berks, UK) at least once daily had no preventive effect on AD (adjusted relative risk: 0.95; 95% CI: 0.78–1.16; *p* = 0.61). Similarly, Skjerven et al. (11) conducted a study (2 × 2 factorial design) testing two primary prevention strategies (skin care and early food introduction) and showed that an oil bath and application of a moisturizer to the infant's face (Ceridal cream) at least 5 days per week from 0.5 to 9 months of age was not effective in preventing AD. Therefore, unfortunately, these two large RCTs could not confirm the efficacy of moisturizer application for primary prevention of AD. We speculated that these inconsistent findings might be due to different countries and cultures, different moisturizer types, and inadequate adherence in the two large RCTs compared to the previous RCT that reported a preventive effect. The application of high-quality moisturizers in sufficient amounts may effectively prevent the onset of AD in newborns and infants. The efficacy of applying moisturizer is inconsistent regarding primary prevention of AD based on data from previous RCTs. Therefore, the most effective moisturizer type and application frequency for preventing AD development in infants remains unclear.

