### Primary Outcome

Participants will be evaluated for AD at each follow-up visit at 4, 12, 24, and 32 weeks after birth. The primary outcome is the time to the first onset of AD during application of the moisturizer. The time to onset of AD is defined as the number of days between discharge of the newborn and the onset of AD. The UK Working Party's diagnostic criteria (12) will be used as diagnostic criteria of AD.

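### Holm's step-down rule would let the second primary comparison be tested at 5% instead of 2.5%, within the same familywise bound

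*Protocol article*

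**What the plan says.** Statistical Methods for Outcomes puts the primary question as an either-or: "To assess whether group A or group B is more effective than group C in preventing the onset of AD". For this, "we will use two co-primary analyses using the log-rank test for the time to the onset of AD", and "The significance level of each comparison is 2.5"%. The section gives no ordering of the two tests, no step-down and no passing on of unused significance level. It states neither an overall level nor whether the tests are one- or two-sided. Hazard ratios for A against C and B against C are to be reported with 95% confidence intervals.

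Sample Size Calculation sets the size: "A total of 60 participants, with 20 in each group, will be enrolled in this study". It calls the study exploratory, gives feasibility as the basis and states no power. Interim Analyses says none is planned. Trial Status says that recruitment has finished and data are still being collected.

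**The concern.** A fixed 2.5% for each of two tests, either of which can succeed, is plain Bonferroni. For testing, it is dominated by Holm. Both rules require the smaller p-value to reach 2.5%. Only Holm then relaxes the level for the larger one. Under the flat rule, if one regimen has succeeded and the other has p = 0.03, the second is declared not significant, although a rule with the same familywise bound would declare it significant.

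What is at stake is the chance of a formal claim for both Fam's Baby regimens against 2e. The number of infants is fixed by resources, so power cannot be gained by enrolling more, and the decision rule can still be changed cheaply.

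**Working it through.** **Inputs from the protocol article.** Two log-rank comparisons sharing control group C, each at 2.5% (Statistical Methods for Outcomes); 20 per group (Sample Size Calculation), 1:1:1 (Sequence Generation); follow-up to 32 weeks (Primary Outcome).

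**Assumed, because the article gives no figure.** Two-sided tests; 32-week AD risk in group C of 20%, 30%, 40% or 50%; hazard ratios for A and B against C between 0.30 and 1.0. The value 0.48 is borrowed from the earlier trial of 2e against Vaseline as required ("hazard ratio: 0.48, 95% CI: 0.27–0.86", Background and Rationale). It is not an estimate of Fam's Baby against 2e.

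**Step 1: the plan's level.** 0.025 + 0.025 = 0.05, so the stated 2.5% equals 0.05 / 2, the Bonferroni level for an inferred familywise 5%. With independent tests the familywise error would be 1 − 0.975² = 4.94%; the shared control group lowers it a little.

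**Step 2: why Holm keeps the bound.** Let p(1) ≤ p(2).
- Flat rule: reject each comparison with p ≤ 0.025.
- Holm: reject the first if p(1) ≤ 0.025; then, and only then, reject the second if p(2) ≤ 0.05.
- Both hypotheses true: an error needs p(1) ≤ 0.025, as under the flat rule, so the bound is 2 × 0.025 = 0.05.
- One hypothesis true: it is rejected only if its own p-value is at most 0.05, so the bound is again 0.05.

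Neither argument needs independence. The rules differ only when p(1) ≤ 0.025 and 0.025 < p(2) ≤ 0.05. The probability of at least one rejection is therefore identical.

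**Step 3: size of the gain.** 100,000 simulated trials per scenario, exponential onset times, no dropout. Entries are percentages, flat → Holm. The column for one comparison shows A against C; B is the same apart from simulation error.

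| Group C risk | HR, A and B | One given comparison | Both comparisons | At least one (either rule) |
|---|---|---|---|---|
| 20% | 0.48 | 7.1 → 7.8 | 2.2 → 3.6 | 12.2 |
| 30% | 0.48 | 11.5 → 12.8 | 3.8 → 6.6 | 19.1 |
| 40% | 0.48 | 15.7 → 17.8 | 6.2 → 10.3 | 25.3 |
| 50% | 0.48 | 20.4 → 23.0 | 9.0 → 14.3 | 31.8 |
| 20% | 0.30 | 13.3 → 14.8 | 5.9 → 8.9 | 20.7 |
| 30% | 0.30 | 24.1 → 27.1 | 11.6 → 17.6 | 36.8 |
| 40% | 0.30 | 34.5 → 38.6 | 19.2 → 27.7 | 49.5 |
| 50% | 0.30 | 44.9 → 49.9 | 28.7 → 38.8 | 61.0 |

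Consistency check, last row: P(at least one) = P(A) + P(B) − P(both). Flat: 44.9 + 44.8 − 28.7 = 61.0. Holm: 49.9 + 49.9 − 38.8 = 61.0.

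With unequal effects (hazard ratios 0.48 and 0.70), the chance of winning on both moves from 1.2% to 2.1% at 20% risk and from 3.8% to 6.6% at 50%.

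**Step 4: error rates.** With no effect in either group, the familywise error is 4.4% to 4.8% under both rules. If A has hazard ratio 0.48 and B has no effect, false claims for B rise from 2.4–2.6% to 2.7–3.4%, still below 5%.

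**Step 5: check on the level of power.** Schoenfeld's formula is power = Φ(√(D/4) × |ln HR| − z), with expected events D = 20r + 20(1 − (1 − r)^0.48) for group C risk r, and z = 2.241 for two-sided 2.5%.
- r = 0.20: D = 6.03; √1.508 × 0.734 = 0.901; Φ(0.901 − 2.241) = 9.0%.
- r = 0.50: D = 15.66; √3.915 × 0.734 = 1.452; Φ(1.452 − 2.241) = 21.5%.

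These lie close to the simulated 7.1% and 20.4%.

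**Step 6: detection at visits only.** A separate simulation, with onset detected only at weeks 4, 12, 24 and 32 and a group C risk of 28%, gave for both comparisons 3.5% → 5.8% at hazard ratio 0.48 for both and 0.8% → 1.8% at 0.70 for both.

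**The case against.** The strongest reply is that nothing here is wrong. The flat rule is prespecified, controls the familywise error and contradicts no other section. That stands: this is an improvement in efficiency, not the repair of an error.

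Second, the gain is small where effects are plausible. Group C is an active control. A hazard ratio of 0.48 against 2e would already imply about 0.48 × 0.48 = 0.23 against the earlier trial's comparator, if effects multiply; 0.30 would imply about 0.14. At 0.48 each comparison gains only about 1 to 3 percentage points. This also stands, and it limits the weight of the point.

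Third, the premise is inferred. A directional question with 95% intervals could mean one-sided tests at 2.5%. A fix that imposed a two-sided scale would then make the first test stricter. The answer is to write Holm on whatever scale the plan intends; the argument in step 2 holds for either. If co-primary meant that both comparisons must succeed, no split would be needed at all, but the either-or wording of the question points away from that.

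Fourth, a reader might infer that phase III planning hinges on the second p-value. The documents do not say so. The article hopes for a phase III trial based on the results and ties no decision to the number of significant comparisons. A second regimen at p = 0.03 would still be reported with its hazard ratio, interval and Kaplan–Meier curve.

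None of this shows that Holm loses anything against the flat rule on the same scale and within the same bound.

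**Conclusion.** The point holds as a modest improvement. Reading the flat 2.5% as a Bonferroni split of 5%, Holm makes every claim the flat rule makes, and sometimes a second one, with the same familywise bound.

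The absolute gain for winning on both is about 1 to 5 percentage points at hazard ratio 0.48 for both, and 3 to 10 at 0.30 for both. These figures rest on the assumed group C risks and hazard ratios, two-sided tests and no dropout. The dominance of Holm does not rest on them.

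A reader might infer that the present rule is invalid, or that Holm would cure the low power of a trial with 20 per group. Neither follows. The familywise error is controlled now, and the chance of at least one success is the same under either rule.

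**What to change.** Before the final analysis, replace the sentence on the significance level by:

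> The familywise significance level for the two log-rank tests is 5%, controlled by the Holm procedure: the smaller p-value is tested at 2.5% and, if significant, the larger at 5%.

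State the sidedness the plan intends, and do not change it by this edit. Report Holm-adjusted p-values: the smaller is min(1, 2 × p(1)), and the larger is the maximum of that value and p(2). Keep the 95% confidence intervals already specified for the hazard ratios, and label them as not adjusted for multiplicity.

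The change touches no data, visits or sample size. It costs a protocol amendment with the approvals described in the article's section on communicating protocol amendments. It should be dated before the outcome data are analysed by group. With data still being collected and no interim analysis planned, the article's stated status leaves room for that.

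### Wald intervals are prespecified for the Cox hazard ratios with 20 infants per arm; if an arm has no AD case, the interval runs from 0 to infinity even when the log-rank test is significant

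*Protocol article*

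**What the plan says.** All references are to the Protocol article.

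- **Sample Size Calculation:** "A total of 60 participants, with 20 in each group, will be enrolled in this study". The number rests on feasibility. No AD incidence, effect size or event count is assumed.
- **Statistical Methods for Outcomes, test:** "we will use two co-primary analyses using the log-rank test for the time to the onset of AD", at 2.5% for each comparison.
- **Same section, estimate:** "Additionally, the Cox proportional hazards model will be used to estimate the hazard ratios of groups A vs. C and groups B vs. C", with 95% CIs.
- **Same section, interval and ties:** "The CIs will be calculated using the Wald type method". "The exact method will be applied to adjust for tied observation times".
- **Same section, other measures:** Kaplan–Meier AD-free rates are planned for each group. A difference in restricted mean survival time is added only if the proportional hazards assumption is rejected at 10%.
- **Objectives:** the aim is to estimate how well each Fam's Baby regimen prevents AD relative to 2e once daily.

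**The concern.** A Wald interval needs a finite estimate and a log-likelihood that is close to quadratic around it. With 20 infants per arm, and a comparator that the authors already regard as protective, an arm with no AD case is a realistic result. The Cox likelihood then has no maximum, and the Wald limits carry no information.

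The report could then show a co-primary comparison won at 2.5% beside a hazard ratio interval of 0 to infinity. The hazard ratio is the only relative effect measure planned in every case, and the article says that the results should inform a phase III trial. Neither of the other stated rules helps. Exact tie handling does not make a monotone likelihood finite, and the restricted-mean analysis depends on a proportional-hazards test, not on event counts.

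**Working it through.** **Inputs from the article.** 20 per arm; log-rank test at 2.5% per comparison (sidedness not stated, taken as two-sided); 95% Wald limits; visits at 4, 12, 24 and 32 weeks. The sample size is a feasibility figure, so there is no calculation of the plan's own to reproduce.

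**1. The test can win with no case in one arm.** With the pooled-table approximation to the log-rank test, n = 20 per arm, N = 40 and d events in total:

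z = (d_A − d/2)/√V, with V = d·n²·(N − d)/(N²·(N − 1)).

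- 0 vs 5: V = 5·400·35/(1600·39) = 1.122; z = −2.5/1.059 = −2.36; p = 0.018.
- 0 vs 6: V = 6·400·34/(1600·39) = 1.308; z = −3/1.144 = −2.62; p = 0.009.

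The smallest significant splits are 0 vs 5, 1 vs 7, 2 vs 9 and 3 vs 10.

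**2. What the Wald interval does at 0 vs 5.** With all events in arm C, no ties and no early censoring, all 20 infants in A stay at risk, and C has 20, 19, 18, 17 and 16 at risk at the five events. The log partial likelihood is −Σ log(n_Ci + 20·HR). It rises steadily as HR falls to 0, so it has no maximum. A software fit stopped at log HR about −23 with SE about 39,000, and printed a 95% Wald interval of 0 to infinity.

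**3. What other intervals do with the same data.**
- Ordinary profile likelihood: the 95% upper limit solves 2·Σ log(1 + 20·HR/n_Ci) = 3.84. At HR = 0.42 the five logarithms are 0.350, 0.366, 0.383, 0.401 and 0.421. They sum to 1.92, and twice that is 3.84. The upper limit is 0.42 and the lower limit is 0.
- Firth-penalised profile likelihood: estimate 0.08, 95% limits 0.0006 to 0.72, both finite.

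**4. How often an arm has no case.** The control incidence p_C is assumed, because the article gives none. Under proportional hazards P(no case in the Fam's Baby arm) = (1 − p_C)^(20·HR):

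| p_C | HR 0.3 | HR 0.48 |
|---|---|---|
| 20% | 26% | 12% |
| 30% | 12% | 3% |
| 40% | 5% | 0.7% |

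**5. How often, given a significant win.** Simulation of 20 vs 20, exponential onset grouped at the four visits, no dropout, two-sided 2.5%, 40,000 runs per cell. Each cell shows power, then the share of wins with a zero-event arm, then their product (both together):

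| p_C | HR 0.3 | HR 0.48 |
|---|---|---|
| 20% | 12.7%; 74%; 9% | 7.1%; 61%; 4% |
| 25% | 18.8%; 55%; 10% | 9.4%; 40%; 4% |
| 30% | 23.4%; 39%; 9% | 11.4%; 21%; 2% |
| 40% | 34.1%; 13%; 5% | 15.6%; 5%; 0.7% |

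A separate simulation gave shares of similar size: about 70% at 20%, 20–37% at 30% and 3–13% at 40%.

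**6. An illustrative control incidence.** The article quotes 12.8% AD at 4 months, an odds ratio of 3.30 for parental AD, and HR 0.48 for 2e in the previous trial. Odds 0.128/0.872·3.30 = 0.484 give 33% without 2e, and 1 − (1 − 0.326)^0.48 = 17% with it. The 12.8% is a general-population prevalence and not a 32-week incidence in high-risk infants, so this shows only that a low control incidence is possible.

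**7. Coverage.** In simulations, nominal 95% Wald limits covered 96–99% when finite, ordinary profile limits 92–96%, and Firth profile limits 95–97.5%.

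**The case against.** The strongest reply has four parts.

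- **Wald limits are conventional, and a fallback for a non-estimable hazard ratio normally belongs in the SAP, which is not shown.** The absence of a fallback is indeed no finding. The point concerns the method that the article does state: it chose the interval, without condition, and chose the one that breaks down at this sample size.
- **The primary inference is the log-rank test, and the Cox model is additional.** This stands. With 0/20 vs 6/20 the p-value, the event counts and both Kaplan–Meier curves remain. A reader might infer that the trial would then carry nothing into phase III planning; the article does not support that.
- **The frequency depends on assumptions.** This also stands. A reader might infer that a zero-event arm is the likely result whenever the trial succeeds. The article gives no control incidence, and the inference fails at 30% and above for HR 0.3 or weaker. Against an active comparator, effects stronger than HR 0.48 may be optimistic. Where a zero-event arm dominates the wins, wins are rare: at 20% incidence, power is 7–13% for HR 0.48 to 0.3.
- **Alternatives have faults too.** Ordinary profile limits can under-cover, and the plain Greenwood interval for a Kaplan–Meier difference gives a zero-event arm no variance. Both are correct and shape the fix.

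**Conclusion.** The concern holds in a limited form. Prespecifying Wald limits at 20 per arm is a poor choice: with no AD case in one arm they give no usable interval, even when the comparison is significant at 2.5%, and nothing else in the stated methods repairs this.

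The size depends on the unstated control incidence. Among significant wins, a zero-event arm is usual at about 20% or lower, depends on the effect size at 25–30%, and is a minority outcome at 40% or more. A win and a zero-event arm together have a probability of at most about 10% for HR 0.3 to 0.48. These figures assume proportional hazards, exponential onset, no dropout and a two-sided test.

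The damage is confined to the effect-size interval. It deserves correction because estimation is the stated objective and the change is small.

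**What to change.** In Statistical Methods for Outcomes, replace the Wald sentence with Firth-penalised Cox profile-likelihood 95% limits for A vs C and B vs C, and name a tie-handling method that works with the penalised fit.

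If a difference in the 32-week AD-free proportion is added, use an interval that does not collapse at zero events, such as a score-type interval. For 0/20 vs 5/20 with complete follow-up, the plain Greenwood standard error is √(0 + 0.25·0.75/20) = 0.097, all of it from arm C. The score upper limit for 0/20 is 3.84/(20 + 3.84) = 16%, so that arm is not treated as known exactly.

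The cost is one or two sentences, with no new data and no change to design or testing. The interval is less familiar, is slightly conservative with very few events, and may mean giving up exact tie handling. The article reports data collection as still under way, so the change could be made before analysis.

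### The restricted mean survival time contrast is reported only if a low-powered proportional-hazards test rejects, so the hazard ratio will usually be the only between-group effect estimate

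*Protocol article*

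**What the plan says.** All the relevant text is in the protocol article, Statistical Methods for Outcomes.

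Three items are unconditional:
- The primary analysis: "we will use two co-primary analyses using the log-rank test for the time to the onset of AD", each comparison at the 2.5% level.
- A description by group: "For each group, Kaplan–Meier estimates of the AD-free rate will be determined".
- The effect estimate: "the Cox proportional hazards model will be used to estimate the hazard ratios of groups A vs. C and groups B vs. C", with 95% Wald intervals.

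The diagnostic follows: "A test with Schoenfeld residuals will be used to assess the proportional hazard assumption". The last step depends on it: "If a significance level of 10% rejects the validity of the proportional hazards assumption", then "group comparisons using the difference in the restricted mean survival time will be applied as a supplementary analysis of the co-primary analysis".

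The section on additional analyses plans none, so the article gives no other route by which the RMST difference would be reported. Sample Size Calculation sets 20 infants per group on feasibility grounds and states no event count or power.

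**The concern.** The sponsor foresees that hazards may not be proportional and names a suitable contrast for that case. It then makes the contrast depend on a significance test in 40 infants. If that test has little power, the contrast will be absent in most trials where it would help, and a non-significant result may be taken as support for the hazard ratio.

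This matters because the Objectives section sets out to estimate how effective each Fam's Baby regimen is relative to 2e, and the Discussion looks ahead to a phase III trial. The size of the between-group effect is a main product of the study. If protection fades or starts late, one hazard ratio averages over that pattern.

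**Working it through.** **Plan's own figure.** The plan states no power or event count, so there is none to reproduce. 3 × 20 = 60 agrees with the stated total, and each comparison uses 40 infants.

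**Events per comparison (assumption).** The Introduction gives 12.8% AD prevalence at 4 months and an odds ratio of 3.30 for parental history.
- Odds: 0.128/0.872 × 3.30 = 0.484. Risk: 0.484/1.484 = 0.326. Events: 40 × 0.326 ≈ 13.
- Applying the earlier trial's hazard ratio for 2e (0.48) to everyone: 1 − (1 − 0.326)^0.48 = 0.173, so 40 × 0.173 ≈ 7 events.

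These figures only bracket the count: the prevalence is at 4 months rather than 32 weeks, and it already includes infants with a family history. Higher risks were also tried, up to about 22 events.

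**Simulation of one comparison.** Inputs: 20 vs 20, 224 days, constant control hazard, hazard ratio (HR) changing at day 112, continuous onset times, no dropout, 6,000 replicates per scenario. The Schoenfeld-residual score test was run at 10%. The article does not give the time transform, so the range covers Kaplan–Meier to identity. Non-estimable fits count as non-rejections. Mean events are in brackets.

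| HR before → after day 112 | Control risk 25% | Control risk 35% | Control risk 45–50% |
|---|---|---|---|
| 0.48 throughout | 11% (7.6) | 11–12% (10.7) | 10–11% (15.6) |
| 1 → 0.5 | 15% (8.9) | 14% (12.5) | 16% (16.2) |
| 1 → 0.25 | 18% (8.3) | 21–22% (11.7) | 24–27% (17.0) |
| 0.25 → 1 | 18–20% (8.3) | 23–24% (11.7) | 30–31% (17.0) |
| 0.5 → 2 | 23–25% (11.1) | 29–30% (15.3) | 34–36% (19.6) |
| 0.4 → 2.5 | 32–35% (11.8) | 40–43% (16.3) | 52–54% (22.7) |
| 0.25 → 4 | 47–54% (14.1) | 60–66% (19.0) | 76–81% (25.4) |

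At 18% control risk (5.9 events), the 1 → 0.25 and 0.25 → 1 patterns are detected in 15–18% of trials. With HR 1 throughout, rejection is 10–12% at 10 to 20 events.

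**Other change point.** With the change at week 12 and control risk 30% / 50%, rejection is 18% / 23% for HR 0.3 → 1, 20% / 26% for protection only after week 12, and 27% / 41% for 0.3 → 2.

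**Analytic cross-check.** Let d events split evenly over two periods and two arms, the most favourable split. The difference of the two log hazard ratios has SE = √(4/(d/2) + 4/(d/2)) = 4/√d. Power at two-sided 10% is Φ(ln r/SE − 1.645) + Φ(−ln r/SE − 1.645), where r is the fold change in HR.
- r = 4, d = 15: SE = 1.033 and 1.386/1.033 = 1.342, giving 38%.
- r = 4, d = 10 and d = 20: 30% and 46%.
- r = 2, d = 10, 15 and 20: 15%, 18% and 20%.

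**What the RMST adds.** Take control risk 35%, so the control hazard is −ln(0.65)/224 = 0.001923 per day. HR 0.25 → 1 and HR 1 → 0.25 both give a cumulative hazard of (1 + 0.25)/2 = 0.625 times control, and a 32-week risk of 1 − 0.65^0.625 = 24%. Mean AD-free time over 224 days is 182.0 days in control, 204.5 with early protection and 188.7 with late protection. The gains are 22.5 and 6.7 days. The RMST difference separates two patterns that end at the same risk.

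**The case against.** The strongest reply is that little depends on this trigger. The co-primary log-rank tests and their 2.5% levels are unconditional. The RMST is only supplementary, the study is called exploratory, and a prespecified check at a lenient 10% level with a prespecified follow-up is a documented plan. All of this stands and limits the severity.

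Four stronger readings are tempting, and the article does not support them:
- *The hazard ratio will stand alone.* It will not. Kaplan–Meier AD-free estimates, which assume no proportionality, are given for every group. They are not, however, a stated between-group contrast with an interval.
- *The pre-test switches the effect measure or the primary test.* Nothing is switched. The hazard ratios always appear, and the RMST difference is added to them.
- *Whether the RMST appears is close to chance.* The test is weak but not uninformative: rejection rises from about 11% under proportional hazards to above half under strong crossing. The 10–12% under proportionality is essentially the chosen level and is no defect.
- *The event count is a property of the plan.* It is an assumption made here.

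It is also fair to say that the RMST is itself one average. In the simulated 0.25 → 4 crossing at 35% control risk, the early gain and later loss nearly cancel (−1.8 days). The Kaplan–Meier curves, not the RMST, show when protection occurs. The RMST complements the hazard ratio and does not fully describe a changing effect. Its precision at 20 per arm was not examined.

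**Conclusion.** The point holds as a cheap improvement of minor severity. As written, the trigger withholds the only planned between-group contrast that does not rely on proportional hazards in most trials with a moderate departure: roughly 60–85% of them for fading, delayed or moderately crossing effects. Detection passes one half only for strong crossing, such as 0.25 → 4 at about 14–19 events or 0.4 → 2.5 at about 23.

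The size rests on assumed event counts (about 7 to 22), a single change in the hazard ratio, continuous onset times and no dropout. Low power for moderate departures holds over the whole event range, both change points and the time transforms tried. The consequence is limited to how the effect size is interpreted: a non-significant residual test must not be read as evidence of proportional hazards. The primary decision is not affected.

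**What to change.** Delete the condition. State that the difference in restricted mean AD-free time, with its confidence interval, is reported for A vs C and B vs C in every case, beside the hazard ratio and still as a supplementary analysis. Fix the truncation time in advance at 32 weeks, or at the shorter arm's last follow-up if that is earlier. The fallback is needed because the assessment schedule allows the final visit up to 28 days early. Keep the Schoenfeld-residual test as description only, with no analysis depending on it.

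The cost is one more supplementary line per comparison in the results. No data collection, significance level or primary test changes. The Trial Status section reports that data were still being collected, so on the article's own account the change could be made before the analysis.
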